		**STUDY PERIOD**						
		Baseline	Rehabilitation					Evaluation
***TIMEPOINT***		***-t1***	***t1***^***2***^	***t2***	***t3***	***t4***	***t5***	***t6***
*Predictors of adherence*								
Health-related Quality of Life	Short Form Health Survey (SF-12) v1 [34]	x	x	x	x	x	x	
Self-efficacy	General Self-Efficacy Scale (GSES) [35]	x						
Depressive symptoms and anxiety	Hospital Anxiety and Depression Scale (HADS) [36]	x						
Motivation and Stage of Change	Readiness-to-Change Lifestyle Questionnaire and Confidence-to-Change Lifestyle Questionnaire [37]	x						
Fatigue	Fatigue Assessment Scale (FAS) [38]	x						
Physical fitness^1^	FitMáx [26]	x	x	x	x	x	x	
Levels of mental stress^1^	PSS-10 [27]	x	x	x	x	x	x	
System usability	SUS [39]	x						x
Mobile Device Proficiency	Mobile Device Proficiency Questionnaire (MDPQ)-16 [40]	x						
*Clinical data*								
Medication adherence	General Adherence Scale (GAS) [41]	x	x	x	x	x	x	
*Usability*								
Satisfaction and usability	Custom questionnaire based on the customer satisfaction score (CSAT) [42] and single ease questions (SEQ) [43]		x	x	x	x	x	
Self-report chatbot and activity tracker usage	Custom questionnaire based on GAS		x	x	x	x	x	

^1^These questionnaires are also part of the periodic lifestyle assessment

^2^The questionnaires of 't1' will not be asked when a patient is included after intervention

### Sample size calculation and statistical analysis

The sample size is based on the primary objective adherence. Anticipating a dropout rate of 50% at 1 year follow up, 100 patients are needed to estimate this adherence rate with a precision of ± 10% (95% CI = [0.398, 0.601]).

Descriptive statistics will be used to report demographics and baseline characteristics. The primary outcome (i.e., ‘adherence’ based on continued use status at 1-year follow-up) will be analysed as a dichotomous outcome measure. Predictors of adherence status and which factors predict re-hospitalizations related to cardiac disease (i.e., the secondary aims) will be investigated using multiple logistic regression analyses. Predictors continuous outcome measures (e.g., QoL) will be examined using linear regression models. Analysis will be carried out in the statistical software package SPSS (version 24, SPSS Inc.).

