### Study population

Patients scheduled for or recently having undergone coronary artery bypass surgery (CABG), a fractional flow reserve test (FFR) and/or a percutaneous coronary intervention (PCI), an electrophysiology study (EP) and/or radiofrequency catheter ablation (RFCA), a transcatheter aortic valve implantation (TAVI), and/or valve surgery will be considered for participation. We will include a total of 100 patients. Patients included before their intervention will be monitored one week extra (the week prior to the intervention). A complete list of inclusion and exclusion criteria is provided in Table 1.

**Table 1 Tab1:** Inclusion and exclusion criteria for Care-On

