#### Secondary endpoints

The secondary endpoints are:Usability (measured using the SUS, the feedback given by the patients during the phone consults with the research nurse, the quarterly questionnaires and the evaluation interview) and the success rate (percentage of tasks that the patients complete correctly)).Predictors of adherence to the lifestyle monitoring system (demographic and disease characteristics, quality of life, self-efficacy, depressive symptoms and anxiety, motivation, stage of change, fatigue, physical fitness, levels of metal stress, use of a goal tracking functionality, perception of system usability and prior experience with technology. Standardized questionnaires will be used for self-report measures and objective ambulatory measures from the lifestyle monitoring system for objective lifestyle measures).The association between lifestyle behaviour at baseline with clinical outcomes will be examined by evaluating patient clinical records (re-hospitalizations related to cardiac disease) and standardized self-report data (quality of life).

The data will be analyzed using multiple regression analysis. An overview of the questionnaires to be complete by the patients per timepoint for the secondary endpoints is shown in Table 5.

**Table 5 Tab5:** Overview of the assessments of the secondary endpoints of the Care-On study

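### The plan assigns at least 14 candidate predictors of adherence to multiple logistic regression, but about 50 patients in the smaller outcome class support only about five unpenalised terms

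*Protocol article*

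**What the plan says.** The sample size is set for the primary outcome alone: "The sample size is based on the primary objective adherence" and "Anticipating a dropout rate of 50% at 1 year follow up, 100 patients are needed" (Sample size calculation and statistical analysis). The interval offered in support is "95% CI = [0.398, 0.601". Under Study population the article confirms that "We will include a total of 100 patients".

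Adherence at one year "will be analysed as a dichotomous outcome measure". The same section says that predictors of adherence status, and factors that predict cardiac re-hospitalization, "will be investigated using multiple logistic regression analyses", in SPSS version 24.

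The candidates are listed under Secondary endpoints: "demographic and disease characteristics, quality of life, self-efficacy, depressive symptoms and anxiety, motivation, stage of change, fatigue, physical fitness", then mental stress, then "use of a goal tracking functionality, perception of system usability and prior experience with technology". The re-hospitalization aim has its own, shorter set of exposures, namely lifestyle behaviour at baseline.

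The article states no limit on the number of terms, no penalisation, no internal validation and no exploratory label for these analyses.

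**The concern.** The candidate list, the binary outcome, the model family and the number of patients are all stated, and they do not fit together. Ordinary maximum likelihood with only three or four outcomes per term overstates associations and describes the sample better than it describes new patients. Many candidates tested at 0.05 also make a chance finding likely.

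The Discussion section intends the determinants to guide improvement and personalisation of the system. Chance or exaggerated determinants would feed directly into that use.

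**Working it through.** **Inputs.** From the article: N = 100; anticipated dropout 50%; binary outcome; multiple logistic regression; the list of candidates. Assumed: the split into sub-scores, the re-hospitalization count, the benchmark of 10 outcomes per term, and the effect sizes and correlations in the simulations.

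**The plan's own figure.** For 50 of 100, the exact (Clopper-Pearson) 95% interval is 0.3983 to 0.6017, which matches the printed limits apart from truncation of the upper one. The simple normal formula gives 0.5 ± 1.96 × √(0.25/100) = 0.402 to 0.598. It needs 1.96² × 0.25/0.10² = 96.04, so 97 patients, for ±10 points. The primary sample size reproduces.

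**Number of terms.** Counting each construct once: demographics, disease, quality of life, self-efficacy, depressive symptoms, anxiety, motivation, stage of change, fatigue, physical fitness, mental stress, goal tracking, perceived usability, technology experience. That makes 14. With two terms each for demographics, disease and quality of life, the count is 17 (assumption).

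**Outcomes per term.** 50/14 = 3.6 and 50/17 = 2.9. A 50% dropout is the most favourable case: at 30% dropout the ratio is 30/14 = 2.1.

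**What the data support.**
- At 10 outcomes per term, 50/10 = 5 terms. Fourteen terms would need 140 in the smaller class (N = 280), and 17 would need 170 (N = 340).
- A stricter criterion targets an expected shrinkage of 0.9: n = k/[(0.9 − 1) × ln(1 − R²/0.9)]. At 50% prevalence the Cox-Snell R² has a maximum of 0.75. For an assumed Nagelkerke R² of 0.15, R² = 0.15 × 0.75 = 0.1125 and n = 14/(0.1 × 0.1335) = 1048. For 0.30, R² = 0.225 and n = 487. Five terms would need 374 to 174. So five terms is an upper limit at N = 100, not a comfortable number.

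**Chance findings.** With independent tests at 0.05 and no true predictor, 1 − 0.95^14 = 51% and 1 − 0.95^17 = 58%. With five terms, 1 − 0.95^5 = 23%.

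**Simulation of the full model.** n = 100, 50% adherent, standard normal predictors with pairwise correlation 0 or 0.3, 1,500 data sets, Wald tests at 0.05. The last two columns assume three true predictors with log odds ratio 0.5 per SD.

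| Terms | Correlation | Null: any p<0.05 | Null: error per term | Null: mean apparent AUC (true 0.50) | Calibration slope | Inflation of true log odds ratios |
|---|---|---|---|---|---|---|
| 14 | 0 | 57% | 6.1% | 0.71 | 0.39 | 22% |
| 14 | 0.3 | 55% | 6.3% | 0.71 | 0.47 | 21% |
| 17 | 0 | 67% | 6.8% | 0.74 | 0.30 | 24% |
| 17 | 0.3 | 66% | 6.6% | 0.74 | 0.37 | 28% |

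A second simulation of the same model gave 58 to 66%, a slope of 0.39 to 0.32 and inflation of 18 to 24%. For scale, a true odds ratio of exp(0.5) = 1.65 would typically be estimated near exp(0.6) = 1.82 with 20% inflation of its logarithm. A slope of 0.39 means that the fitted log odds would need shrinking to about 39% of their spread to suit new patients.

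**Re-hospitalization.** The article gives no event count. Assuming 10, 15, 20 or 30 events and about five baseline lifestyle domains (activity, diet, stress, sleep, smoking), the ratios are 10/5 = 2, 15/5 = 3, 20/5 = 4 and 30/5 = 6 events per term. Simulated at nominal rates of 10% to 30%, with two true predictors and correlation 0.3, the calibration slope is 0.48 to 0.74.

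**The case against.** The strongest objection is that the article lists candidates, speaks of regression analyses in the plural, and never says that every candidate enters one model. Selection and shrinkage are commonly left to an analysis plan, which is not shown here. This stands, and the simulated figures are therefore conditional on the full model. It does not remove the point. Splitting the list over several models, or screening it first, still tests 14 or more candidates against about 50 outcomes. What would cure it is a short pre-specified list or penalisation, and the article states neither.

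Four stronger readings are tempting, and the documents do not support them:

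- *The plan will produce false predictors.* At 55 to 67% this is somewhat more likely than not, and only if nothing is real. Most of it is ordinary multiplicity, since the error per term is only 6 to 7%.
- *Re-hospitalization is the same model with far fewer events.* No event rate is given, and that aim concerns baseline lifestyle behaviour, not the adherence list.
- *The model's discrimination is invalid.* The article announces no risk score and no AUC. The inflated odds ratios matter more for the stated aim.
- *The binary outcome should be replaced by the adherence percentage.* Adherence status at one year is the declared primary endpoint, so modelling its predictors is coherent. One third of the general adherence rate is completion of quarterly assessments, which is not naturally defined in most four-week windows. Filling in zeros after dropout, with 50% dropout expected, would give an outcome dominated by zeros.

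**Conclusion.** The point holds for the adherence model, as a matter for the secondary aims. On the article's own figures, at least 14 candidates face about 50 outcomes, at most 3.6 per term, and this does not depend on whether the count is 14 or 17. If all enter one unpenalised model, expect log odds ratios inflated by roughly 20%, a calibration slope of about 0.3 to 0.5, and a 55 to 67% chance of at least one nominally significant predictor when none is real.

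These sizes rest on the assumed effects and correlations and on ordinary maximum likelihood, which is the natural reading because no penalisation is mentioned. For re-hospitalization the conclusion is weaker: the model is likely to be thin, by an amount that cannot be fixed without an event count. The primary objective and its sample size are unaffected.

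**What to change.** In Sample size calculation and statistical analysis:

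1. For adherence, either name about five predictors in advance or fit the full list with penalisation (Firth or ridge). Firth mainly corrects small-sample bias; ridge also shrinks for overfitting and suits the full list better. Validate the model internally by bootstrap in either case.
2. Label all other predictor results exploratory, and make no significance claims for them or control multiplicity. Testing the remaining candidates one at a time at 0.05 would bring the chance of a false finding back to 51 to 58% over 14 to 17 tests.
3. For re-hospitalization, use a penalised model or cap the number of terms according to the events observed.
4. If wanted, add a regression on the adherence percentage as supportive, with its handling of dropout and of the quarterly component defined. The binary endpoint stays as declared.

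The cost is a change of wording and a modest amount of analysis, possibly with software beyond SPSS 24. The main model will hold fewer predictors and show less striking associations. No extra patients, visits or data are needed.

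### Fourteen named predictors of adherence go into multiple logistic regression with at most 50 patients in the smaller outcome class, so jointly fitted odds ratios would be overstated and apparent fit optimistic

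*Protocol article*

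**What the plan says.** The Secondary endpoints section gives the candidate list. It opens with "demographic and disease characteristics, quality of life, self-efficacy, depressive symptoms and anxiety, motivation, stage of change, fatigue, physical fitness" and continues with mental stress, use of goal tracking, perceived usability and prior experience with technology. It says that the data will be analysed by multiple regression.

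The section Sample size calculation and statistical analysis says that one-year adherence status "will be analysed as a dichotomous outcome measure". Predictors of that status, and of cardiac re-hospitalisation, "will be investigated using multiple logistic regression analyses". On the number of patients it states: "The sample size is based on the primary objective adherence". The reasoning is "Anticipating a dropout rate of 50% at 1 year follow up, 100 patients are needed", for a precision of ±10% and a 95% interval of 0.398 to 0.601. The Study population section confirms the total: "We will include a total of 100 patients".

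The article therefore fixes the candidate list, the model family and the sample size. The sample size was chosen without regard to the predictor models.

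**The concern.** Maximum likelihood logistic regression has a known small-sample defect. When there are few events per coefficient, the estimated log odds ratios lie too far from zero on average, and the model appears to discriminate better in its own data than it does in new patients. Several of the named constructs probably overlap (depressive symptoms, anxiety, perceived stress, fatigue, quality of life), which makes the individual estimates less stable still.

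Finding determinants of adherence is a named secondary aim, and the Discussion intends to use them to improve and personalise the system. At stake is whether a reported determinant is real and of about the stated size.

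**Working it through.** **1. The plan's own figure.** For a proportion p = 0.5 and half-width d = 0.10, n = z²p(1−p)/d² = 1.96² × 0.25 / 0.01 = 96.04, so 97, close to the planned 100. The exact (Clopper-Pearson) 95% interval for 50 of 100 is 0.3983 to 0.6017, which matches the stated interval up to truncation. The primary calculation is sound.

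**2. Count of predictors** (Secondary endpoints). The constructs are demographics, disease characteristics, quality of life, self-efficacy, depressive symptoms, anxiety, motivation, stage of change, fatigue, physical fitness, mental stress, goal tracking, usability and technology experience: 14. If demographics are only age and sex (one extra coefficient) and the three disease groups take two terms (one more), there are 14 + 1 + 1 = 16 coefficients. The 16 is an assumption; the 14 is a count.

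**3. Events per coefficient.** At the anticipated 50% dropout the split is 50 to 50. This is the best case, because the smaller class of 100 cannot exceed 50.
- 50/14 = 3.6
- 50/16 = 3.1

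**4. Bias and optimism.** Assumptions, none of them stated in the article: n = 100, 50% outcome, all predictors entered jointly, three true predictors with log odds ratio 0.50 per SD and the rest null, pairwise correlation 0 or 0.3.

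| Quantity | Truth or new patients | As it would be reported |
|---|---|---|
| Log odds ratio, maximum likelihood | 0.50 | 0.62 to 0.67 |
| Log odds ratio, Firth | 0.50 | 0.51 to 0.53 |
| AUC, maximum likelihood | 0.64 to 0.70 | 0.80 to 0.84 |

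The inflation is 0.62/0.50 to 0.67/0.50, or 24% to 34%. Firth estimation also cuts the mean squared error of the coefficients by about 35% to 40%. With 16 coefficients the calibration slope of the maximum likelihood model in new patients is 0.32 to 0.42, where 1 is ideal.

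**5. False predictors.** With k independent tests at an assumed 5% and no true effect, the chance of at least one false predictor is 1 − 0.95^k.
- k = 14: 1 − 0.95^14 = 51%
- k = 16: 1 − 0.95^16 = 56%

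Simulation at n = 100 gives 55% to 58% with 14 coefficients and 60% to 65% with 16, because the per-test error is about 6.4% and not 5%. At n = 1,000 with 16 coefficients it is still 56% to 59%. Most of this risk is therefore multiplicity, and the sparse data add only a little.

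**6. Would variable selection help?** With 14 candidates and either three true odds ratios of 1.5 or two of 2.0, backward elimination or univariable screening still gives at least one false predictor in 19% to 55% of data sets. A selected true odds ratio of 1.5 appears as 1.9 to 2.2, and an identical second study selects the same set in 3% to 19% of cases. The number of candidates drives the problem, whichever route is taken.

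**The case against.** The strongest reply is that the article does not commit to a single full model. It speaks of analyses in the plural, and entry rules, shrinkage and internal validation are commonly left to an analysis plan, which is not shown. This stands in part: joint entry by maximum likelihood is an inference, and silence on shrinkage is no fault in itself. The mismatch between list, model family and sample size is nevertheless fixed in the article, and step 6 shows that the usual selection routes do not remove it.

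It is also fair that this is a secondary aim with no confirmatory claim or decision rule attached.

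A reader might infer more than the article supports:
- **That the sparse data cause the false predictors.** They mostly do not (step 5), and Firth estimation does not reliably cure them. With its penalised likelihood-ratio test and 16 null predictors, the chance of at least one false finding was still 56%.
- **That a continuous adherence outcome would suffer the same inflation.** It would not. Least-squares coefficients are unbiased at this ratio; imprecision, optimistic fit and multiplicity would remain.
- **That the regression is meant to produce patient profiles.** The Discussion mentions profiles in connection with lifestyle data and personalised care, not as an output of this model. No risk score is announced, so the AUC and calibration figures matter only if model fit is reported.
- **That the re-hospitalisation model is certainly worse.** The article gives no event rate. The same concern applies if events number fewer than 50, but its size cannot be stated.

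**Conclusion.** The point holds in a limited form. Fourteen named constructs, multiple logistic regression and 100 patients leave about 3 to 3.6 events per coefficient at best. If the predictors are entered jointly by maximum likelihood, log odds ratios would be overstated by about a quarter to a third under the assumed effects, and the apparent AUC would exceed its value in new patients by roughly 0.15. Determinants are unlikely to replicate well; to say that they cannot replicate would go too far. The chance of at least one false predictor, 51% to 56% or more, is a separate matter of multiplicity.

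The counts come from the article. The effect sizes, the correlations, the 5% level, the 16 coefficients and joint entry are assumptions. The primary adherence estimate and its sample size are not affected. The change is worth making because the better method is cheap and uses the same data.

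**What to change.** In Sample size calculation and statistical analysis:

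1. Estimate the adherence and re-hospitalisation models by penalised logistic regression: Firth for reported odds ratios, or ridge with a cross-validated penalty if prediction is the aim.
2. Wherever model fit is reported, give the bootstrap optimism-corrected AUC and calibration slope, for example from at least 500 samples.
3. Label the determinants exploratory and make no claim from single p-values. This step is essential, because Firth estimation alone does not control the false-predictor rate.

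A shorter pre-specified list would work in the same direction. With 5 candidates the simulated calibration slope was about 0.71, against about 0.40 with 14, but named constructs would have to be dropped.

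The cost is one paragraph of analysis text and a few hours of programming, outside the named SPSS version if that lacks the method. The odds ratios will be smaller and fewer determinants will reach significance. No new patients or data are needed, and the change can be made at the analysis stage.

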### Outcome measures

#### Primary endpoint

The primary outcome is adherence providing self-tracking data, which is calculated as the total number of participants that completed the study at one year follow-up divided by the number who started using the system at baseline. Secondly, the general adherence rate and individual adherence rates of the chatbot, the quarterly assessments and wearing the health watch are compared. Adherence classifications and a dropout threshold were set up to adequately categorize patient’s adherence (see next section ‘Adherence classification and dropout threshold’). Other measures of adherence will also be explored (i.e., adherence rates per quarter, the success rate (percentage of the tasks that the patients complete correctly)).

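### Quality of life is measured at up to six visits with 50% dropout anticipated, yet only linear regression is named; a mixed model over all visits would be safer

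*Protocol article*

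**What the plan says.** Under Secondary endpoints, the article makes the association of baseline lifestyle with later outcomes a secondary aim. One of the two outcomes is "standardized self-report data (quality of life"; the other is cardiac re-hospitalization, taken from clinical records. That section names multiple regression for the secondary endpoints. The section Sample size calculation and statistical analysis adds that "Predictors continuous outcome measures (e.g., QoL) will be examined using linear regression models".

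Table 5 schedules SF-12 at baseline and at t1 to t5, which is up to six measurements. A footnote removes t1 for patients included after the intervention.

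On numbers, Study population states "We will include a total of 100 patients", and the sample size section says "The sample size is based on the primary objective adherence". It continues "Anticipating a dropout rate of 50% at 1 year follow up". The primary outcome is defined as the "total number of participants that completed the study at one year follow-up divided by the number who started using the system at baseline". Quality of life also appears under Secondary endpoints as a candidate predictor of adherence.

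**The concern.** The outcome is measured repeatedly, the plan itself expects heavy loss by one year, and the only model named is one that takes a single outcome value per patient. Neither plain reading of it serves the aim well.

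- **One regression on 12-month SF-12.** Patients without that score drop out of the analysis, and their earlier follow-up scores do not help to estimate the 12-month association.
- **One regression on scores pooled over visits.** Correlated scores from the same patient would be treated as independent.

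The first reading is the more natural one for a long-term outcome. It loses precision. It also loses validity if those who stay differ in both quality of life and lifestyle. The protocol treats that as possible: quality of life, mental stress and physical fitness are all listed as candidate predictors of adherence. The estimated association could then describe the patients who stayed and not the cohort.

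**Working it through.** **1. The plan's own figure.** Inputs from the sample size section: p = 0.50, half-width d = 0.10, 95% confidence. n = 1.96² × 0.50 × 0.50 / 0.10² = 96.04, so 97 against 100 stated. The exact (Clopper-Pearson) interval for 50 of 100 is 0.3983 to 0.6017, which agrees with the stated 0.398 to 0.601 apart from truncation. The figure reproduces. It concerns adherence only; no precision or power is given for quality of life.

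**2. Patients with a 12-month score.** If dropout means no 12-month SF-12: 100 × (1 − 0.50) = 50. If some of those who stop still return it, the number lies between 50 and 100. The documents do not settle where.

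**3. Precision at those numbers.** The protocol gives no effect size for this association, so r = 0.3, two-sided 5% and 80% power are assumptions.
- Standard error with 50 patients relative to 100: √(100/50) = 1.41.
- Detectable correlation, r = tanh[(1.960 + 0.842)/√(n − 3)]: 0.39 for n = 50, 0.33 for n = 70, 0.28 for n = 100.
- Power at r = 0.3, Φ[atanh(0.3) × √(n − 3) − 1.960]: 56% for n = 50, 86% for n = 100.

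This is the cost of missing scores. A mixed model recovers only part of it (step 5).

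**4. Bias.** Simulation with assumed inputs: 100 patients; standardized lifestyle x; standardized QoL at baseline, an interim visit and 12 months; true slope on x of 0.30 at each visit; residual correlation 0.6 between visits. The probability of a 12-month score is logistic in interim QoL and x, with about half observed. The all-visit analysis is a likelihood analysis that treats all three QoL scores as outcomes.

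| Weights on interim QoL, lifestyle | 12-month regression slope | All-visit slope |
|---|---|---|
| 0, 0 (dropout unrelated) | 0.30 | 0.30 |
| 1, 0.5 (same direction) | 0.23 | 0.30 |
| 2, 1 (same direction, stronger) | 0.15 | 0.30 |
| 2, −1 (opposite directions) | 0.34 | 0.30 |

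Dropout that depends on lifestyle alone leaves the regression slope at 0.30. Dependence on interim QoL alone pulls it down, but less than when lifestyle acts in the same direction. The sign of the bias therefore depends on the dropout mechanism.

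**5. Precision gained.** Standard deviation of the estimated slope over repeated trials of 100, in the first three rows: 0.139, 0.141 and 0.147 for the 12-month regression against 0.124, 0.127 and 0.136 for all visits. That is roughly 0.14 to 0.15 against 0.12 to 0.14.

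**6. Role of baseline SF-12.** In this set-up lifestyle is also related to baseline QoL. Conditioning on baseline QoL changes the full-data slope to 0.30 − 0.6 × 0.30 = 0.12. That answers a different question (change given the starting level), so where baseline SF-12 enters the model matters.

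**The case against.** The strongest reply is that the article does not commit to a poor analysis; it is merely brief. A reader might infer that quality of life will be analysed in about 50 completers by ordinary regression, ignoring baseline and interim SF-12. The text does not say so. It fixes no outcome time point and no completer-only rule, and multiple regression can carry baseline SF-12 as a covariate. Covariates and missing-data rules may stand in an analysis plan that is not shown, and their absence is no fault.

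Nor is 50% dropout shown to mean 50% missing SF-12. The figure is anticipated for the adherence outcome. Non-adherence as defined in the adherence section is a classification from a composite rate, nothing says that such patients stop receiving questionnaires, and the research nurse reminds patients every quarter. That SF-12 is filled in through the platform is plausible but not stated: Table 4, the list of periodic lifestyle questionnaires, does not include it.

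A reader might also infer that the bias runs toward zero. The candidate predictors are listed without direction or strength, and opposing influences push the slope upward. The recovery of 0.30 by the all-visit analysis is partly built in, because the simulated dropout depends only on observed values.

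All of this stands and limits the claim. What remains is that the article does name a method, and that method does not suit its own visit schedule and dropout assumption.

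**Conclusion.** The concern holds in conditional form. The protocol names only linear (multiple) regression for an outcome scheduled up to six times, with half the cohort anticipated to drop out. If that means a 12-month regression, between about 50 and 100 patients would contribute, and the slope would be biased if staying in depends on both quality of life and lifestyle. Under the assumed inputs, the slope ranges from 0.15 to 0.34 around a true 0.30, with no bias if dropout is unrelated to quality of life. These sizes illustrate the risk; the documents give no figure for how strongly dropout depends on either factor.

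This affects a secondary association in a study sized for adherence alone. The primary outcome and its sample size are untouched. The change is worth making because it is cheap and protects against a loss that the plan itself foresees.

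**What to change.** In the statistical analysis section, replace linear regression for quality of life with a linear mixed model for SF-12 that uses all observed visits from all enrolled patients, with t1 only where it is scheduled. Include visit, baseline lifestyle and lifestyle × visit, and report the lifestyle contrast at 12 months as the estimate.

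Keep baseline SF-12 among the outcomes, so that the estimate remains the total association of baseline lifestyle with 12-month quality of life. If an association with change is also of interest, report a model adjusted for baseline SF-12 as a separate analysis, labelled as such. State that the main analysis assumes dropout depends on observed data.

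The cost is a change of wording and slightly more analysis work; SPSS, the package already named, has a mixed-model procedure. No new data collection is needed. The limits should be plain: the model does not protect against dropout that depends on unobserved scores, and the gain in precision is modest (slope SD about 0.12 against 0.14 under the assumed values).
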